## **Theoretical Frameworks**

The Gate Control Theory and Lazarus and Folkman's theory provide the theoretical underpinning of this study [26-27]. The gate control theory suggests that peripheral nerves

become excited when cells are damaged. Impulses from nerves pass along to spinal cord systems and other neuroanatomical structures before reaching the cerebral cortex where pain is perceived. The gate control system in the spinal cord opens and closes to modulate pain perception. If non-nociceptive input (IVR) exceeds the nociceptive (pain) input, then the gate can partially or entirely close, blocking the transmission of the pain signal to the brain. The theory also proposes that pain signals that descend from the brain through the gate can be amplified by emotional experiences, such as anxiety and stress. Lazarus and Folkman's theory [27] states that an individual's evaluations of anxiety and stress-provoking experiences are influenced by their perceptions of control over a potential threat. Providing information may help improve pediatric patients' sense of control over a procedure [18-19, 28].

In the context of these two theories, IVR functions by providing multisensory input to divert the children's conscious attention from venipuncture-associated pain, thus helping close gate control and decreasing pain perception [29]. The analgesic effects of IVR have been supported by the results of functional magnetic resonance imaging assessment [30]. Providing procedural information through IVR modules further help increases the children's sense of control over the procedure, thereby reducing their stress and anxiety, as well as pain signals transmitted through the gate control system. Therefore, IVR intervention will likely reduce pain, anxiety and stress; these changes are evidenced by physiological changes in the heart rates and salivary cortisol levels of the patients. Thus, patients may show increased procedural compliance, consequently decreasing the length and cost of the procedure while possibly improving the satisfaction of the health-care providers with the procedure [5, 10].

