#### **Sample size – Patients**

In 2016, about 250 hospitalized patients aged between 4 years to 12 years were admitted to the unit and required venipuncture. Sample size estimation was based on the effect estimated from a previous IVR study using the FPS-R Scale as a primary outcome measure [11]. By using the power analysis software, GPower 3.1, it was estimated that a sample size of 85 participants per group would enable a 2-arm RCT to detect a between-group difference of 0.8 in FPS-R scale with a pooled standard deviation of 1.84 with 80% power at 5% level of significance. Taking into account of up to 15% attrition rate [24], 200 children will be recruited. Furthermore, to account for those who fail in the first attempt of venipuncture, the total sample size is adjusted to 250 children to be recruited with the estimation of 20% of unsuccessful cases in the first attempt. As such, the total recruited number of children will be 250 for the experimental and control groups, with 125 children in each group.

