#### **Implementation Protocol**

The venipuncture procedure will be conducted in the treatment room while parents/ legal guardians wait outside. Patients assigned to the intervention group will receive IVR intervention prior to the start of venipuncture until the end of the procedure [11, 23]. The RA will provide simple and standard instruction on how to use the equipment. The headset will then be placed on patient’s head and adjusted to ensure a comfortable and secure fit. Patients will be allowed to view the IVR module according to their age group (4–7 years, 8–12 years). During the intervention, the control of the IVR module will only be achieved by the head movement of the patients. The patients will also be told that the intervention will be discontinued if they experience motion sickness, eye discomfort, or headaches.

After receiving IVR intervention, the RA will invite the doctor/phlebotomist to start the venipuncture. The beginning of the procedure is indicated by doctor/ phlebotomist disinfecting the venipuncture site. The RA will note the time of first attempt at venipuncture. The end of the procedure is indicated by application of band aid to the venipuncture site. The RA will remove the IVR equipment from the child after the procedure. The protocol follows for the first venipuncture attempt only. If the first attempt is unsuccessful, additional attempts occurring after the protocol will be completed, but participants will be counted as unsuccessful case of the study.

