## **Data analysis**

IBM SPSS 24 will be used for data analysis. Continuous demographic and clinical variables will be presented as their means and standard deviations, whereas categorical data (e.g. sex) will be presented in frequencies and percentages, as appropriate. The intention-to-treat principle will be adopted for the outcome comparisons between the intervention and control groups. The generalized estimating equations (GEE) model will be used to compare each of the outcome measures across the time points between the two groups. GEE model can account for intra-correlated repeated measures data and produce unbiased estimates even if there are missing data, provided that the data are missing at completely random. Cohen's d values will be calculated to estimate the effect sizes of the IVR intervention on the outcome variables. All statistical analyses are two-sided and level of significance will be set at 0.05.

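### The sample size budgets first-attempt failures out of the evaluable sample after randomisation, which conflicts with the stated intention-to-treat principle

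*Protocol*

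**What the plan says.** Children are randomised after consent and baseline assessment and before the procedure (Protocol, Randomization; Data Collection Procedures). Implementation Protocol confines the study procedures to the first attempt. If that attempt fails, further attempts may follow, but "participants will be counted as unsuccessful case of the study".

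Sample size – Patients starts from 85 per group, goes to 200 in total for up to 15% attrition, and then adds a separate step: "to account for those who fail in the first attempt of venipuncture, the total sample size is adjusted to 250 children", with failure put at 20%.

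Data analysis states: "The intention-to-treat principle will be adopted for the outcome comparisons between the intervention and control groups". It adds that GEE estimates are unbiased with missing data on condition that the data are missing completely at random.

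Theoretical Frameworks gives a reason why failure may depend on arm. After describing how IVR should reduce pain, anxiety and stress, it continues "Thus, patients may show increased procedural" compliance, with a shorter and cheaper procedure as the result.

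No section says whether children with a failed first attempt stay in the analysis, or how their later outcomes are measured.

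**The concern.** First-attempt failure happens after randomisation. If children are removed because of it, the comparison is between two groups selected by something the intervention may have changed, and randomisation no longer protects it. The protocol's own theory expects IVR to alter how well children cooperate. It is also plausible, though the protocol does not say so, that failure is more common in distressed or moving children, who would tend to report more pain. Loss on that basis is unlikely to be missing completely at random, which is the condition the protocol sets for its GEE.

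The outcomes exposed are those measured during or after the attempt: FPS-R (the primary outcome), anxiety, heart rate, cortisol, length of procedure, staff satisfaction and cost-effectiveness. Outcomes not collected from these children on the day cannot be recovered later.

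**Working it through.** **Inputs.** From Sample size – Patients: "between-group difference of 0.8 in FPS-R scale", "with a pooled standard deviation of 1.84" and "with 80% power at 5% level of significance"; attrition 15%; first-attempt failure 20%. From Data analysis: "All statistical analyses are two-sided and level of significance will be set at 0.05". Allocation is 1:1 (Randomization).

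**1. The plan's own figure.**
- Standardised difference: 0.8 / 1.84 = 0.435.
- Two-sample t-test, two-sided 0.05, 80% power: 84.01 per arm, rounded up to 85. Power at 85 per arm is 80.5%.
- Attrition: 170 / 0.85 = 200.
- First-attempt failure: 200 / 0.80 = 250.

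The stated 250 reproduces exactly, so the arithmetic is sound.

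**2. What the 250 implies.** Working back, 250 × 0.80 × 0.85 = 170, which is 85 per group. Failures number 250 × 0.20 = 50. If they were analysed, 170 / 0.85 = 200 would be enough and the last step would serve no purpose.

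**3. Possible bias in a success-only comparison.** The documents give no figures for this, so the following are assumptions: pain has SD 1.84; a latent normal propensity to fail has correlation r with pain; a fraction p fails; the true difference between arms is zero. The mean shift among successes in one arm is −1.84 × r × φ(c) / (1 − p), where c is the (1 − p) normal quantile. The ratio φ(c) / (1 − p) is 0.195, 0.274, 0.350, 0.424 and 0.497 for p = 10%, 15%, 20%, 25% and 30%. The bias is the difference in shift between arms:

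| Failure in the two arms | r = 0.2 | r = 0.5 | Share of 0.8 |
|---|---|---|---|
| 20% v 20% | 0 | 0 | 0 |
| 25% v 15% | 0.05 | 0.14 | 7% to 17% |
| 30% v 10% | 0.11 | 0.28 | 14% to 35% |

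For example, 25% v 15% with r = 0.5 gives 1.84 × 0.5 × (0.424 − 0.274) = 0.14. If failure is less common on IVR, the error masks a benefit. If it is more common on IVR, the error creates a false one.

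**4. Power if failures are kept.** 250 × 0.85 = 212.5, about 212 analysed or 106 per arm.
- If the SD of 1.84 already covers children with failed attempts, power is 88.3%.
- If 1.84 describes successes only and failures (20%) score g points higher, the SD becomes √(1.84² + 0.20 × 0.80 × g²). For g = 2 the SD is 2.01 and power is 82%. For g = 3 the SD is 2.20 and power is 75%. The values of g are assumptions.

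**The case against.** The strongest reply is that the protocol never says these children are excluded. It counts them as unsuccessful, adopts intention-to-treat explicitly, and may define the analysis set in a statistical analysis plan that is not shown. It is true that exclusion is an inference. But the rule and the sample-size budget are fixed in this document, and the second inflation has no function unless these children are lost. An unseen plan that kept them would still leave the sample-size section in conflict with the analysis.

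The reply also has force against several stronger readings that a reader might infer:

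- **A large bias of known size.** A 10-point difference in failure rates times a 3-point pain gap gives 0.3 points, 38% of 0.8. But 3 points is 3 / 1.84 = 1.6 SD, and at 20% failure the latent-normal model would need a correlation of about 0.93 to produce it. The documents support no such figure.
- **Keeping failures must raise power to 88%.** This holds only if 1.84 covers them. With a 3-point gap added to a success-only SD, power falls to about 75%, below the planned 80%.
- **The longest procedures are the ones removed.** Length of procedure runs from disinfection to the band aid, and the protocol covers the first attempt only. On that definition a failed attempt need not be long.
- **The rule hides any effect on first-attempt success.** Failures are counted, so a tally by arm would be possible. The protocol simply does not commit to reporting it.
- **The headset makes failure more likely.** The Intervention section says the modules need little head and hand movement so that the procedure is not hindered. The support for dependence on arm is the expected gain in compliance, and even that passage does not mention first-attempt success.

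Confining measurement to the first attempt is also a defensible aim, because a reading 30 minutes later could reflect repeat punctures. That argues for a careful choice of anchor, not for leaving children out.

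**Conclusion.** The concern holds as a conflict between the sample-size section and the first-attempt rule on one side and the intention-to-treat statement on the other. About 50 of 250 randomised children are budgeted as non-contributing because of a post-randomisation event that may depend on arm and on distress. A success-only comparison can therefore be biased and is unlikely to meet the protocol's own missing-data condition.

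The conflict itself follows from the protocol's figures and needs no outside assumption. The size of the bias does: the range from zero to about 0.28 FPS-R points rests on the assumed failure rates, the correlation of 0.2 to 0.5 and the latent-normal model, and the sign depends on which arm fails more. It would be wrong to conclude that the trial's result must be biased, or in which direction. The conflict should be resolved before recruitment, while the outcomes can still be collected.

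**What to change.** Reconcile Sample size – Patients, Implementation Protocol and Data analysis as follows.

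- Make the primary analysis include all randomised children in their assigned arm.
- Collect the outcomes for children whose first attempt fails as well. Needle insertion (T1) occurs either way.
- Use one consistent anchor. Keep the definitions of length of procedure, T2 and T3 tied to the end of the first attempt, and state what marks that end when the attempt fails. Record whether further attempts took place before T3. Report total time to the last attempt only as an additional measure.
- Report first-attempt success by arm.
- Keep the success-only comparison as a labelled sensitivity analysis.
- Restate the sample size as 250 recruited, 15% attrition and about 212 analysed (106 per arm). Give power of about 88% only on the condition that the SD of 1.84 covers children with failed attempts, and show the lower values if it does not (about 82% for a 2-point pain gap, 75% for 3 points).

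The cost is a protocol amendment and outcome recording for about 50 children who are in the trial anyway, with a possibly larger SD. No extra patients are needed, and the clinical handling of repeat attempts is untouched.

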### **Fidelity of the Intervention**

The fidelity of the intervention will be ensured by recruiting a RA with a minimum of two years of experiences in pediatric care. She will undergo two days' training conducted by the lead PI. The training will include (1) basic knowledge about and application of IVR; (2) procedures of implementing the intervention and collecting data; and (3) management of untoward reactions, such as motion sickness. A minimum of one session conducted by the RA each month will be randomly selected to assess compliance with the implementation protocol by the lead PI. The lead PI and RA will meet monthly to discuss the delivery of IVR intervention and study progress. Feedback will be given accordingly.

### **Outcome Measures**

#### **Primary outcome**

***Faces pain scale-revised:*** The FPS-R scale is a 0 to 10 scale comprising six horizontally arranged cartoon faces with expressions of “0 = no pain” to “10 = very painful” [39]. Participants will be asked to point to the face that indicates how much pain she/he feels. The protocol for use of FPS-R is standardized and is a reliable and valid scale for evaluating pain in children [9, 11].

## Secondary outcomes

**Visual analogue scale for anxiety:** A visual analogue scale (VAS) for anxiety will be used to assess the anxiety levels of children aged 4–7 years old. The VAS is a 10 cm horizontal line marked with the words "not worried" (low score) at one end and "very worried" (high score) at the other, with different facial expressions drawn along the line. Children aged between 4 and 7 will be asked to indicate their levels of anxiety by moving a pointer over the line, with higher scores indicating greater anxiety. The VAS is a widely used scale which is reliable and valid for measuring the subjective feelings of children [40]. It has been used previously by PI to assess the anxiety level of children undergoing medical procedures [41].

**State anxiety scale for children:** The short form of the Chinese version of the State Anxiety Scale for Children (CSAS-C) will be used to measure the anxiety levels of children aged 8-12 [42]. The CSAS-C is a 3-point Likert scale with total scores ranging from 10 to 30. Higher scores indicate greater anxiety levels [41]. The psychometric properties of the short form has been tested and found to correlate strongly with the full form ( $r = 0.92$ ). It has good internal consistency ( $r = 0.83$ ) and convergent validity that differentiate the anxiety state of children under various situations [43]. The PI has previously used it to assess the anxiety level of children undergoing medical procedures with Cronbach's alpha 0.80 to 0.88 [41].

**Heart rate:** The heart rate of the children will be measured by a standard automatic heart rate monitoring machine (available in the study institution) to assess the physiological responses of children. Heart rate is considered to be objective and definitive in indirectly assessing physiological responses of pain and anxiety of children [23-24].

**Salivary cortisol assay:** Saliva cortisol assay will be used as to assess the stress levels of the children [44]. The trained RA will collect saliva samples from the patients using the Salivette sampling devices, according to the manufacturer's instructions at 10 min prior and 30 min after the venipuncture procedures [44]. Collected saliva samples will be frozen at  $-80^{\circ}\text{C}$

until further processing and analysis. Cortisol levels in the saliva samples will be measured using an enzyme-linked immunoassay kit (Salimetrics, PA, USA), according to the manufacturer's instructions.

**Length of procedure:** A standard stop watch will be used to measure the length of the procedure from the beginning (time when the doctor/phlebotomist starts to disinfect the site) to the end of procedure (time when applies the band aid on the venipuncture site).

**Staff satisfaction scale:** The staff satisfaction scale will be adopted to measure the satisfaction levels of the health care providers toward the procedure [45]. It consists of 8-item and each rated by a 5-point scale ranging from 1 = strongly disagree to 5 = strongly agree. Higher score presents a higher level of the satisfaction. This scale has been translated by the PI using back-translation method recommended by Brislin (1970) and used in a previous study with the Cronbach's alpha of 0.90 [41].

**Cost-effectiveness:** Cost analysis will be examined based on incremental cost-effectiveness ratio expressed as incremental cost per every one unit decrease in the primary outcome of the FPS-R scale immediately post-intervention with respect to the baseline. All the cost data involved will be expressed in Hong Kong dollars and valued on the starting date of the study on the basis of non-subsidized cost. All costs incurred will be estimated per each participant using the method of Thompson & Barber [46]. Specifically, the cost of human resources (e.g. doctors, nurses, phlebotomist, and health care assistants) is measured by the salary of the middle rank of the professionals and calculated based on the minutes used to perform the procedures. Costs of consumables to perform the venipuncture (e.g. alcohol pad, glove, butterfly needles, and band aid) will be based on the retail price paid by the finance office of the hospital. In addition, the cost for development of IVR modules and VR goggles will be included in the intervention group.

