### **Hypotheses for testing:**

- (1) Compared with standard care, IVR intervention significantly reduces pain, anxiety, stress, and length of procedure in pediatric patients undergoing venipuncture;
- (2) Compared with standard care, IVR intervention significantly improves the satisfaction of health care providers toward the venipuncture procedures;
- (3) IVR intervention is significantly more cost-effective than standard care for pediatric patients undergoing venipuncture.

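### Staff time is costed only for the venipuncture itself, so the labour of delivering IVR is understated, and the ICER as specified does not test hypothesis (3)

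*Protocol*

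**What the plan says.** **Costing rule** (Protocol, Secondary outcomes, Cost-effectiveness). The general statement is broad: "All costs incurred will be estimated per each participant". The detail that follows is narrower. Staff are introduced as "the cost of human resources (e.g. doctors, nurses, phlebotomist, and health care assistants" and their cost is "calculated based on the minutes used to perform the procedures". Venipuncture consumables are added. For the IVR arm, "the cost for development of IVR modules and VR goggles will be included in the intervention group".

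**What counts as the procedure.** Length of procedure, in the same section, starts at the "time when the doctor/phlebotomist starts to disinfect the site" and ends when the band aid is applied. The Implementation Protocol uses the same two markers.

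**When IVR is delivered** (Implementation Protocol). "The RA will provide simple and standard instruction on how to use the equipment". The headset is then fitted and the child views the module. Only after that does the research assistant (RA) call in the doctor or phlebotomist. The RA takes the equipment off once the procedure is over.

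**Hypothesis and statistic.** Hypothesis (3) is that "IVR intervention is significantly more cost-effective than standard care for pediatric patients undergoing venipuncture". The statistic is an ICER, the "incremental cost per every one unit decrease in the primary outcome of the FPS-R scale immediately post-intervention with respect to the baseline". Data analysis names generalized estimating equations (GEE) across the time points, two-sided at 0.05, and says nothing specific to cost-effectiveness.

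**The concern.** Labour is central to this comparison. The Abstract faults the existing combination of distraction and information for the manpower and time it takes, and the Immersive Virtual Reality section presents IVR as needing no extra staff. Yet a trained RA instructs each child, fits the headset and removes it. If those minutes are not counted, one arm's costing assumes part of what the analysis is meant to show.

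This cannot be repaired at the analysis stage. Length of procedure is the only duration the protocol plans to record. The RA also notes the time of the first attempt, but that does not show when IVR began or ended. If set-up and removal are not timed during the trial, the data will not exist.

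The second issue is a mismatch between claim and statistic. Hypothesis (3) is listed for testing and uses the language of significance, but the protocol gives no criterion by which a ratio of cost to pain reduction would be judged significant.

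**Working it through.** The cost-effectiveness text contains no cost total, delivery time or threshold, so there is no figure of the plan's own to reproduce on this point. The labour issue is settled by comparing passages; the arithmetic below only illustrates scale.

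**1. IVR activities against the costing rule**

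| Activity in the IVR arm | Position relative to disinfection–band aid | Duration recorded? | Listed as a cost? |
|---|---|---|---|
| Instruction by RA | Before | No | No |
| Headset fitting | Before | No | No |
| Viewing before the procedure | Before | No | No |
| Viewing during the procedure | Inside | Yes, as length of procedure | Only for staff performing the procedure |
| Headset removal by RA | After | No | No |
| Module development, goggles | Not time-based | n/a | Yes |

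Applied as written, the rule counts little or none of the delivery labour.

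**2. Possible size of the uncounted labour**

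Assumptions, not in the documents: 3–10 minutes per child at HK$1–4 per minute. From the protocol: planned FPS-R difference 0.8 (Sample size – Patients) and headset price about HK$15 (Immersive Virtual Reality).

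- Added cost per child = minutes × rate: 3 × 1 = HK$3 to 10 × 4 = HK$40.
- Added to the ICER = cost ÷ 0.8: 3/0.8 = HK$3.75 to 40/0.8 = HK$50 per FPS-R unit.
- Goggles alone: 15/0.8 = HK$18.75 per unit.
- Uncounted labour relative to goggles: 3/15 = 0.2 to 40/15 = 2.7 times.

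So labour could be small beside a cost item the protocol does include, or well above it.

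**3. Does the ICER answer hypothesis (3)?**

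The illustration borrows the sample-size inputs, so I checked those first. A difference of 0.8, SD 1.84, 80% power and two-sided 5% give 84 per group by the normal formula and 84.01, hence 85, by the t-test. Then 170/0.85 = 200 and 200/0.80 = 250. The stated 85, 200 and 250 reproduce.

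- Standard error of the FPS-R difference with 85 per group: 1.84 × √(2/85) = 0.282.
- 95% interval if 0.8 is observed: 0.8 ± 1.96 × 0.282 = 0.25 to 1.35.
- Assume a fixed cost difference of HK$15. The ICER is 15/0.8 = HK$18.75. Over that interval it runs from HK$11.1 to HK$60.8.
- Net benefit at threshold λ = λ × 0.8 − 15, with standard error λ × 0.282:

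| λ (HK$ per FPS-R unit) | Net benefit (HK$) | z |
|---|---|---|
| 10 | −7 | −2.48 |
| 20 | 1 | 0.18 |
| 50 | 25 | 1.77 |
| 100 | 65 | 2.30 |

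With identical data, IVR is significantly worse value at HK$10, undecided at HK$20 and HK$50, and significantly better at HK$100. The verdict depends on λ, which the protocol does not state. Treating the cost difference as known is a simplification; its sampling error would add further uncertainty.

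GEE does not fill the gap. It compares repeated outcomes between groups over time, whereas the ICER is one ratio formed from two between-group differences.

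**The case against.** **The costing text may be wider than its detail.** It opens by promising all costs, the staff list is only illustrative, and the disinfection-to-band-aid definition sits under a different outcome. This partly stands. A reader might infer that IVR labour is deliberately excluded or valued at zero, and the text does not say that. But the open list widens who may be costed, not which minutes are counted. The same start and end markers appear in the Implementation Protocol, and no other duration is planned.

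**Inference for hypothesis (3) may be left to the analysis plan.** Thresholds, intervals and net benefit are commonly specified there, and that plan is not shown. The protocol also cites a paper on analysing cost data in randomised trials, though it attaches the citation to estimating cost per participant. This also stands in part. It would be too strong to say that the trial's data cannot test hypothesis (3): per-child costs and FPS-R scores would support a net-benefit test. What remains is that the protocol states a significance hypothesis and pairs it with a statistic that, as specified, does not test it.

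**Two further inferences are not supported.** One is that the ICER will be negative and so uninterpretable. The Theoretical Frameworks section expects a shorter and cheaper procedure, but the costing then adds development and goggles to the IVR arm. Total incremental cost may therefore be positive, and a negative ratio is only a possibility. The other is that development cost will be spread over the trial's children, making the ratio depend on trial size. The protocol states no allocation basis.

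**Conclusion.** The point holds in a limited form. Following the stated costing rule understates the labour cost of the IVR arm, because most delivery work falls outside the counted minutes, is not timed and is not among the listed IVR costs. That favours IVR on the labour component. The HK$3–40 per child is an illustration on assumed minutes and wage rates, not an estimate.

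A reader might go further and conclude that the whole cost comparison is tilted towards IVR. The documents do not support that: development cost is charged to the IVR arm, its amount and allocation are not given, and it works in the opposite direction. The net direction of error in total incremental cost is not established.

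On hypothesis (3), an ICER without a threshold or interval does not, as specified, test the claim, and the GEE model does not supply the missing criterion.

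This concerns one secondary outcome. It should be corrected before recruitment mainly because the missing minutes cannot be recovered later.

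**What to change.** 1. In the IVR arm, record staff minutes from first headset instruction to headset removal. Include them in the per-child cost at the grade of staff who would deliver IVR in practice. If that person is already costed during the procedure, count only the minutes outside it, to avoid double counting.

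2. For hypothesis (3), choose one of two routes. Either report incremental net benefit (threshold × FPS-R reduction attributable to IVR, minus the cost difference) with bootstrap intervals over a stated range of thresholds, or reword the hypothesis as estimation of incremental cost and effect.

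The cost is one extra stopwatch reading for each IVR child (125 at full recruitment), a small addition to the data form, and some analysis. The downside for the sponsor is a less favourable cost figure for IVR. Sample size, randomisation and the primary analysis do not change.

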## **Immersive Virtual Reality**

Immersive virtual reality (IVR) may help overcome the above obstacles. It provides a means of human/computer interaction, wherein a human becomes an active participant in a

virtual environment created through a head-mounted display [20]. The user is immersed and actively participates in the virtual environment as it changes in real time with the user's movements [21]. Moreover, it can be used at any time and place in clinical settings without requiring extra manpower. Thus, it can be easily provided as an intervention for patients. IVR modules can also be tailored to provide health information to the user. The cost of IVR equipment has also become increasingly affordable. For instance, the price of a commercially available disposable IVR headset (VR Goggles) is only about HK \$15. Distraction-based IVR intervention has already been implemented in the Lucile Packard Children's Hospital at Stanford in the United States [22].

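### The staff time that delivers IVR outside the disinfection-to-band-aid window is neither recorded nor costed, so the incremental cost of IVR is understated by that labour

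*Protocol*

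**What the plan says.** Three parts of the protocol bear on this.

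- **The clock.** Under Secondary outcomes, length of procedure runs "from the beginning (time when the doctor/phlebotomist starts to disinfect the site") to the end ("time when applies the band aid on the venipuncture site"). Implementation Protocol gives the procedure the same beginning and end.
- **The cost rule.** The Cost-effectiveness paragraph of Secondary outcomes opens with a general statement that all costs will be estimated for each participant, and then specifies how. It values "the cost of human resources (e.g. doctors, nurses, phlebotomist, and health care assistants") at the salary of the middle rank, "calculated based on the minutes used to perform the procedures". It adds consumables for the venipuncture in both arms. For the IVR arm it adds module development and goggles. The result is an incremental cost per one-unit fall in FPS-R from baseline to immediately after the intervention.
- **How IVR is delivered.** Implementation Protocol states: "The RA will provide simple and standard instruction on how to use the equipment". The headset is then placed and adjusted, and the order of events is explicit: "After receiving IVR intervention, the RA will invite the doctor/phlebotomist to start the venipuncture". The RA takes the equipment off after the procedure. Fidelity of the Intervention says delivery is secured by "recruiting a RA with a minimum of two years of experiences in pediatric care", with two days of training.

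The only times the protocol says will be noted are the first venipuncture attempt (Implementation Protocol) and the length of procedure (Data Collection Procedures).

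**The concern.** Instructing the child, fitting the headset, running IVR before disinfection and removing the headset are all work by a trained person. By the protocol's own definitions they fall outside the minutes on which staff are costed. The RA is not named among the costed staff, and no IVR-specific line covers delivery. Standard care, including its explanation to the child, goes to both arms, so nothing in the control arm offsets the omission.

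Hypothesis 3 says IVR is more cost-effective than standard care, and the background presents the cost result as an aid to decisions about routine use. It also says that IVR can be used "without requiring extra manpower". A cost rule that gives delivery labour no value cannot test that statement. At stake are the numerator of the cost-effectiveness ratio and any later claim that a shorter procedure saves staff time.

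**Working it through.** **No stated figure to reproduce.** The documents give no delivery time, staff salary or cost. The sample size does reproduce (85 per group for a difference of 0.8 and SD of 1.84; 170/0.85 = 200; 200/0.80 = 250, so 125 per arm). Only the 125 and the 0.8 are used below.

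**Step 1: which tasks are inside the costed window?**

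| Task | Arm | Position | Costed? |
|---|---|---|---|
| Disinfection to band aid | both | inside | yes |
| Instruct child on equipment | IVR only | before | no |
| Place and adjust headset | IVR only | before | no |
| IVR viewing before the operator is invited | IVR only | before | no |
| Remove headset | IVR only | after | no |
| Module development, goggles | IVR only | not a time item | yes |

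**Step 2: direction.** Let *m* be the delivery minutes outside the window per IVR child and *w* the salary per minute of the person delivering IVR. The control arm has no such minutes.

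Incremental cost on a full count = incremental cost as planned + *w* × *m*

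The planned figure is too low by *w* × *m* for any *m* above zero, whatever the other costs are.

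**Step 3: illustrative size.** Assume *m* = 2 to 10 minutes. Baseline is nominally taken 10 minutes before the procedure, and allocation is revealed only after baseline data are obtained, so the top of the range is not far-fetched. It remains an assumption.

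- 125 × 2 / 60 = 4.2 staff-hours
- 125 × 10 / 60 = 20.8 staff-hours

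If the FPS-R difference equals the planning value of 0.8, the ratio omits *m*/0.8 worker-minutes per unit: 2/0.8 = 2.5 to 10/0.8 = 12.5.

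**Step 4: could a booked saving be misleading?** Suppose two costed staff are in the room (an operator plus one assistant, from Setting and Participants) and IVR shortens the window by *s* minutes. As planned, the change in staff-minutes is −2*s*. With delivery counted it is *m* − 2*s*.

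| *s* | *m* | As planned | With delivery |
|---|---|---|---|
| 0.5 | 10 | −1 | +9 |
| 1 | 3 | −2 | +1 |
| 1 | 10 | −2 | +8 |
| 2 | 2 | −4 | −2 |
| 2 | 3 | −4 | −1 |

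The sign changes only when *m* > 2*s*. Both values are assumed, so a reversal is possible but not shown.

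**The case against.** **The cost text may be broad enough.** It opens by covering all costs, and its staff list is given as examples, so the RA's minutes might be meant to count. This leaves a little room, but the next sentences narrow the rule to procedure minutes, consumables, development and goggles. The protocol also provides for no collection of delivery minutes.

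**A later analysis plan could settle it.** A plan can settle valuation, but it cannot supply times that nobody wrote down. A typical delivery time could be estimated from the monthly observed sessions and used in a sensitivity analysis. That would help, but it is not per-child data, which the cost method calls for.

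**The RA is research staff.** This is right for consent, questionnaires and saliva sampling, which should stay out of the cost. Instruction, fitting and removal are delivery, and someone would have to do them in routine care.

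A reader might also infer four stronger claims that the documents do not support.

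- *Procedure length is biased toward IVR.* The clock is identical in both arms. It tests what hypothesis 1 and Theoretical Frameworks propose, namely that better compliance shortens the needle procedure.
- *Total room time rises.* The protocol makes no claim about room time, and the gap from baseline to procedure is nominally 10 minutes in both arms. A room-time outcome would largely reflect the research schedule.
- *The overall cost result must favour IVR.* Development and goggles are charged to IVR alone, so the net direction is unknown.
- *The manpower phrase under Immersive Virtual Reality must be withdrawn.* It is background and enters no analysis.

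**Conclusion.** The point holds for the cost evaluation only. As written, the plan leaves out labour that occurs in one arm, so the incremental cost of IVR is understated by the value of that labour. This rests on reading the costed minutes through the protocol's own definition of the procedure, which is the natural reading though not spelled out in the cost paragraph. The size cannot be computed from the document. The 4 to 21 staff-hours follow from an assumed 2 to 10 minutes per child for one worker and 125 children. The primary outcome, the clinical secondary outcomes and procedure length are unaffected. This is an inexpensive improvement to a secondary evaluation, best made before recruitment because per-child times cannot be recovered afterwards.

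**What to change.** 1. Have the RA record two further clock times for each IVR child: the start of IVR instruction or fitting, and headset removal.
2. In the Cost-effectiveness paragraph, state that IVR-delivery minutes outside the disinfection-to-band-aid window are costed in the IVR arm, at the mid-rank salary of the ward worker who would deliver IVR in routine care. State that research tasks (consent, questionnaires, saliva sampling) are excluded.
3. Keep disinfection to band aid as the length-of-procedure outcome and report delivery minutes beside it. Do not present a shorter procedure alone as a saving in total staff time.

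The cost is two entries on an existing form and a few sentences of protocol text. The downside for the sponsor is a less favourable cost figure for IVR.
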